#### Retention and adherence

To ensure adherence and retention throughout the entire study period, participants will be contacted regularly via telephone or email and will be provided with information about their appointments. A few days prior to the intervention, a member of the study team will call the participant to remind them of the upcoming appointments and to check if there are any open questions to address. Additionally, the participants will be provided with a document listing all their appointments with notes regarding parking and caffeine consumption at pre-assessment. At the end of each visit, the participants will be reminded of the date and time of the next session. Throughout the whole study period, participants will be encouraged to contact the 24/7 study answer machine if questions or concerns arise. Similarly, they will be prompted to leave a voice message if they are unable to attend or wish to reschedule a session. They then will be contacted to discuss alternative scheduling or to address possible questions and concerns. At the end of the study, participants will receive a reasonable financial reimbursement (approximately 10 € per hour) and the results of their neuropsychological screening and, if they underwent MRI scanning, their structural MRI on a compact disc. If complete adherence to the protocol is not possible, any effort to collect as much data as possible will be made.

### Data management and monitoring

All participant data will be pseudonymised. Spreadsheets containing both participant IDs and personal data will be protected with a password only known to the study staff and will be stored on a secure file server. Similarly, digital data, that is, output files from computer-based tasks, will be saved on a secure file server directly after acquisition. Non-digitally acquired data will be manually digitalised by a staff member of the research team and double-checked by another member. Progress of data entry and checking procedures will be documented. As additional quality control, we implemented systematic quality control by checking for outliers or missing values in key outcomes on a weekly basis and cross-checking 100% of critical documents (consent forms, adverse events). Additionally, protocol adherence is further monitored through equipment logs and weekly team meetings. Files containing subject records will be sorted by participant ID and stored securely. Sensitive data, such as names and medical records, will be scored separately in lockable cabinets in rooms with access restricted to the researchers. Protocols of the tDCS setup of each participant and session will also be stored on the file server, and MRI data will be pseudonymised before analysis. Following good scientific practice, data will be stored for at least 10 years.

### Adverse events monitoring

Safety and tolerability will be assessed through monitoring any potentially occurring adverse events (AEs) via an adverse events questionnaire,^34^ administered at the end of each training week (V4, V7 and V10). We will refrain from administering the AE questionnaire at every visit, since this would possibly draw the participant’s attention to minor sensations during the stimulation and would only serve as a distraction from the training task. Generally, adverse events during tDCS are rare and minimal. Known AEs with the applied stimulation parameters (20 min, 2 mA) are skin reddening, a tingling sensation under the electrode sites and occasionally a mild headache.^34^ As we will be using a local anaesthetic under the electrode sites, we expect even less noticeable sensations.^88 89^ Investigators will be instructed to monitor AEs and serious AEs (SAEs) throughout the study and document all detected AEs and SAEs. Participants will be informed at baseline assessment about all possible AEs and risks and can withdraw their consent at any time without providing a reason. In case an SAE occurs, the study physician will first make an assessment as to whether a causal relationship with the intervention is considered plausible. If more than three of the enrolled participants suffer from SAEs likely to be associated with the intervention (as assessed by the study physician), the trial will be discontinued.

## Statistical methods

The primary outcome, percent of correct responses in the n-back task at post-training compared with the pre-training assessment, will be analysed using ANCOVA with post-assessment n-back performance as dependent variable, pre-assessment n-back performance as covariate and group allocation (target intervention (n=26) vs control intervention (n=26)) as independent variable. Linear mixed models will be conducted for secondary outcomes with experimental group as a between-subjects factor. All models will be corrected for age and performance at pre-assessment. We will use random intercept models that account for the clustering of measures within individuals. In case of violation of requirements for parametric methods, data will be transformed before analysis. Analyses of primary and secondary outcomes will be reported in detail in the statistical analysis plan to be written and registered before unblinding of investigators performing the analyses. Confirmatory analysis of treatment effects will be conducted within an intention to treat (ITT) framework with multiple imputed data sets in case of missing data (under the assumption of missing completely at random or missing at random). Further as sensitivity analyses, we will perform ‘per protocol’ analyses, including only those participants who finished post-assessment. Feasibility data (% drop-out rate and number of attended training sessions per participant) will be analysed using descriptive statistics. Data distributions of the feasibility questionnaire items will be visually assessed for normality using q-q plots and statistically using the Shapiro-Wilk test.^90 91^

Data analysis will be conducted using IBM SPSS Statistics for Windows (IBM, Armonk, New York, USA), MatLab (The Mathworks, 2016) and R software (https://www.R-project.org).

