#### Secondary outcomes

Secondary outcome will be working memory performance in the untrained task (n-back,^48^ at follow-up assessment, operationalised by the percentage of correct responses). The n-back task (1-back and 2-back) will assess working memory by requiring participants to indicate via keypress whether the current digit matches the one presented ‘n’ steps earlier. This untrained task evaluates updating, discrimination and decision-making processes (detailed methods in Neuropsychological assessment). Additionally, performance in the primary memory training task (LU task)^49^ and visuospatial memory performance (virtual reality (VR) task)^50^ will be assessed at post and follow-up assessments. Performance in the training task will be operationalised by number of correctly recalled lists in the LU task, and visuospatial performance will be operationalised by number of correctly recalled items in the VR task.

Further secondary outcome measures include quality of life, operationalised via the PROMIS Preference score (PROPr score) which serves as a summary scoring system of health-related quality of life including domains such as depression, fatigue, pain interference and ability to participate in social roles and activities.^51^ The domain of cognitive function will be scored separately because it is the most important subscale for this study. Scoring will be carried out according to the scoring manuals (http://www.healthmeasures.net/). Feasibility will be operationalised through drop-out rates (% participants that did not complete post-assessment), adherence rates of training sessions (number of training sessions attended) and the post-study system usability questionnaire (PSSUQ),^52^ completed by study assessors. Additionally, structural and functional neural correlates (assessed at pre-assessments and post-assessments), as measured by structural and functional MRI, will be assessed.

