### Methods: randomisation and blinding

#### Randomisation

Allocation of the participants to the experimental groups will be performed by a researcher not involved in the study. Participants will be randomly allocated in a 1:1 ratio to the two groups (anodal vs sham tDCS). Baseline performance in the n-back task will be used as strata (two performance strata; ≤87% correct and >87% correct in the n-back task). This 87% cut-off was empirically derived from prior studies using identical n-back paradigms,^59^ ensuring balanced distribution of high-performing and low-performing individuals across groups while maintaining sensitivity to detect stimulation and training effects at the group level. Randomisation blocks with varying block sizes will be generated for each of the two stimulation groups, using R software (https://www.R-project.org) and the blockrand package (http://CRAN.R-project.org/package=blockrand). Participants will then be allocated to the anodal or sham tDCS group based on the generated randomisation sequences within each block and stratum.

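### The covariate rule for the secondary models leaves out either the n-back stratification factor or, on a second reading, each outcome's own baseline; on the first reading the loss is conservative and about 0 to 8% of interval width

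*Protocol article*

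**What the plan says.** **Allocation.** Under Randomisation, the protocol article allocates 1:1 in blocks within two strata: "Baseline performance in the n-back task will be used as strata", split at 87% correct. Table 1 schedules the n-back task at V1, V11 and V12 but not at V0, so the stratifying value is presumably the V1 score.

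**Models.** Under Statistical methods, the primary ANCOVA takes "pre-assessment n-back performance as covariate". For the rest, "Linear mixed models will be conducted for secondary outcomes with experimental group as a between-subjects factor". One rule then covers everything: "All models will be corrected for age and performance at pre-assessment". No stratum term is named. The pre-assessment term is not defined outcome by outcome. Further detail is deferred to a SAP that is to be registered before unblinding.

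**Outcomes.** The Secondary outcomes section lists n-back at follow-up, LU ("Performance in the training task will be operationalised by number of correctly recalled lists in the LU task"), the VR task, the PROPr score and a separately scored PROMIS cognitive-function domain. Table 1 shows LU, the VR task and PROMIS all measured at V1, so each of these outcomes has its own pre-assessment value.

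**The concern.** Stratified allocation removes part of the between-stratum difference from the comparison of the groups. If the stratum also predicts the outcome, the treatment estimate varies less from trial to trial than under simple randomisation. A model without the stratum cannot see this: it returns the between-stratum variance to the residual and reports too large a standard error. Intervals are then too wide and tests reject too seldom.

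The concern is most plausible for LU, because the document describes both LU and n-back as tasks of working-memory updating. It is least plausible for PROPr, a quality-of-life summary. The secondary estimates have some weight because the trial is meant to inform the planning of later confirmatory trials, and the value needed is already collected.

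**Working it through.** **1. The plan's own figure.** Inputs from Sample size: d = 0.7, two-sided alpha 0.10, power 80%. The normal approximation gives 2 × (1.645 + 0.842)² / 0.7² = 25.2, so 26 per arm. The exact t-test gives 25.94, so 26 per arm with power 80.1%. Allowing for 13% dropout, 52 / 0.87 = 59.8, so 60. Both stated figures reproduce, and this point does not touch them.

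**2. Which models carry the stratifier.**

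| Outcome | Term read as own V1 value | Term read as n-back |
|---|---|---|
| n-back, post and follow-up | n-back in, own baseline in | the same |
| LU, VR, PROPr, PROMIS cognitive function | n-back **out**, own baseline in | n-back in, own baseline **out** |

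For the second row, each reading omits one useful V1 value.

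**3. Size on the first reading.** The documents give no association between n-back and these outcomes, so it is varied. Simulation assumptions: N = 52; permuted blocks of 2, 4 or 6 within two strata; a median split, because the share of women on each side of 87% is not given; own baseline correlated 0.4 with n-back; own baseline and age in every model; a single post value; 90% intervals; 8,000 runs per row. The partial correlation is that of continuous n-back with the outcome, given own baseline.

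| Partial correlation | Width, stratum omitted / included | Type I error, omitted | Type I error, included |
|---|---|---|---|
| 0 | 0.998 | 0.096 | 0.094 |
| 0.1 | 1.001 | 0.096 | 0.096 |
| 0.2 | 1.010 | 0.096 | 0.099 |
| 0.3 | 1.027 | 0.092 | 0.100 |
| 0.4 | 1.049 | 0.084 | 0.098 |
| 0.5 | 1.083 | 0.078 | 0.102 |

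The Monte Carlo standard error near 0.10 is √(0.1 × 0.9 / 8000) = 0.0034. The 0.096 in the first three rows is therefore not distinguishable from nominal, while 0.078 clearly is.

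**4. Check by formula.** A median split correlates √(2/π) = 0.798 with a normal variable. Given own baseline, the stratum's share of the partial correlation is 0.798 × √0.84 / √(1 − (0.798 × 0.4)²) = 0.731 / 0.948 = 0.77. The expected width ratio is 1 / √(1 − (0.77ρ)²), which is 1.028 at ρ = 0.3 and 1.08 at ρ = 0.5. The simulation gave 1.027 and 1.083.

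**5. Is the reported standard error itself wrong?** At partial correlation 0.5, the model without the stratum gives a mean half-width of 0.3541. Dividing by t = 1.677 gives a standard error of 0.211, against a true sampling SD of 0.1974: about 7% too large. With the stratum, 0.3269 / 1.678 = 0.195 against 0.1948, which agrees. The sampling SD hardly differs between the two models (0.1974 and 0.1948), so what is lost is mostly in the reported standard error.

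**6. Cost if n-back is unrelated.** At partial correlation 0, squared half-widths rise by (0.3544 / 0.3536)² − 1 = 0.5% with the stratum, and by (0.3557 / 0.3536)² − 1 = 1.2% with continuous n-back. The usual allowance of one degree of freedom in about 48, some 2%, is an upper figure here.

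**The case against.** **The reading is not settled.** The same section names n-back as the pre-assessment covariate for the primary outcome. If the general rule carries that meaning, the stratifier is in every model. This stands, and it is why the point is put in two branches. It does not rescue the sentence: on that reading the LU, VR and PROMIS models lack their own V1 values.

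**The SAP may supply the detail.** It is not shown, and a stratum term is ordinary SAP content. This limits the point but does not remove it, because the article states a covariate rule for all models instead of staying silent.

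**The intervals may not be too wide.** A reader might infer that they are too wide as a matter of fact. The documents do not support that: they report no correlation between n-back and any other outcome, and with no residual association the width ratio is 0.998. Scenarios that start from a strong association overstate the likely effect, above all for PROPr and the VR task. For LU, a V0 measurement also exists alongside V1.

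**The 10% level is borrowed.** It is stated only for the primary outcome, and no level is given for secondary outcomes. The error rates above illustrate calibration; they are not the plan's own operating characteristics.

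**Conclusion.** The point holds in conditional form. As written, the covariate rule omits one V1 value from the LU, VR, PROPr and PROMIS cognitive-function models. On the natural reading that value is the factor the trial randomises by. The excess width is then negligible up to a partial correlation of about 0.2 (1% or less), about 3% at 0.3, and 5 to 8% at 0.4 to 0.5.

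These sizes rest on the assumed correlations, a median split and a single post value. The same mechanism is expected for the group effect in the repeated-measures model, but that model was not simulated. An uneven split at 87% would carry less of the n-back information and shrink the effect. The loss on the second reading was not sized.

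A reader might go further and infer bias, inflated false positives or damage to the primary result. None of these follows. The error is conservative, the primary ANCOVA and n-back at follow-up already contain continuous pre-assessment n-back, and the sample size reproduces. This is a cheap improvement, not a flaw that threatens the trial's conclusions.

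**What to change.** Replace the general covariate sentence, or define it in the SAP before unblinding, so that each model for LU, the VR task, PROPr and the PROMIS cognitive-function domain contains group, the outcome's own V1 value, age, and V1 n-back. The n-back term can be the continuous score or the 87% stratum. The continuous score recovers more if the relation is roughly linear: at partial correlation 0.5, omitting it widens intervals by 15%, against 8% for the stratum. Choose one form in advance. The n-back models need no change.

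The change takes one sentence and no new data. The downside is the single degree of freedom where n-back proves unrelated to the outcome, about 2% of variance at n = 52.

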### Patient and public involvement

We will conduct a brief semistructured interview at the last visit (V12) to assess the patients’ satisfaction with the trial and answer any upcoming questions. The patients were not involved in designing the intervention. All patients will be informed about the study details (eg, the experimental group they participated in) on completion of the study.

## Ethics and dissemination

The study was approved by the ethics committee of the University Medicine of Greifswald ((BB236/20), date of first approval: 5 January 2021) and will be conducted in accordance with the Helsinki Declaration. All data collected will be pseudonymised. Results of the study will be made accessible to scientific researchers and healthcare professionals via publications in peer-reviewed journals and presentations at national and international conferences. Furthermore, the scientific and lay public can access the study results on the ClinicalTrials.gov website (identifier: NCT04817566).

### Protocol amendments

Any substantial amendment to the study protocol will be submitted to the Institutional Ethics Committee for review and approval.

### Confidentiality

The collected data will be treated as confidential. Direct access to personal information and source data documentation will only be given to study monitors, study assessors, and the research team.
